## **9. Assessment of Safety**

### **9.1 Potential Risks and Benefits**

For participants without obesity, there is no direct benefit for participation in this study, but the information obtained will be used in scientific research and may be helpful to the participant or others in the future. For participants with obesity, individuals may lose weight, which may lower risk for other illnesses. The list that follows includes anticipated risks. There may also be other risks that are not known at this time.

#### **9.1.1 Privacy:**

All PHI will be kept securely on Duke servers behind a firewall and with many layers of protection. Additionally, some PHI and participants' responses will be kept confidential in a HIPAA-compliant Data Server hosted in Amazon Web Services by Mytonomy. Although we will make all the efforts to keep all the study information confidential, there is a risk that someone could get unauthorized access to RESILIENCE Study data. Taking part in the study requires the use of one or more of an external study websites, mobile applications, messaging, devices, and email. Because some of these systems are developed and managed externally, there is no guarantee that they are free of risk.

#### **9.1.2 Venipuncture:**

Mild and transient local pain, mild bruising, fainting or lightheadedness, and a small risk of infection are potential consequences of the routine venipuncture that will be used for blood sample collection. A small number of individuals may have a vasovagal response to blood draws.

#### **9.1.3 Radiation Exposure:**

Individuals undergoing CAC testing will be exposed to very low degree of radiation. The radiation exposure to a participant will be detailed in the consent.

#### **9.1.4 Exercise:**

Exercise may be recommended as part of the weight loss intervention. Muscle strains, sprains, tripping, and falling can result from physical activity.

#### **9.1.5 Women with Reproductive Potential**

Because being pregnant affects diet and women, women who are pregnant or planning a pregnancy in the short-term will not be allowed to participate in this study. Women of childbearing potential will have a urine pregnancy test conducted at Duke Clinic Lab at the baseline clinic visit and it must be negative in order to participate in the study. Women who meet at least one of the following criteria will be excluded from the pregnancy screen:

- Age > 55 years old
- 12+ months since last menstrual period
- 6+ months since last menstrual period + FSH > 40 IU
- Hysterectomy
- Bilateral salpingectomy
- Bilateral oophorectomy
- Female partners
- Male partner incapable of fathering children (vasectomy NOT included)

To stay in the study, women will need to use effective methods of birth control, as outlined in the consent form. Women who become pregnant during the study will need to notify the study team immediately and be withdrawn from the study.

## 9.2 Monitoring

The progress of the study will be monitored to ensure that it is conducted in accordance with the protocol and applicable study and regulatory requirements. Study monitoring by the study PI will include reviewing the integrity of the clinical study data and visiting the study site periodically to observe visits and compliance with study protocol.

## 9.3 Event Definitions and Reporting

This is a minimal risk intervention and it is highly unlikely that we will encounter any adverse events (AE) or serious adverse events (SAE). However, our study team will review, collate, and evaluate adverse events in real-time. The PI will evaluate all adverse events within 72 hours; serious adverse events will be evaluated within 24 hours. Any study-related serious adverse event will be reported the Duke IRB within 2 weeks; all others will be included in the annual report. We will compile an aggregate AE report annually. Given the nature of the intervention, we would expect the rate of AEs to be low. In the present study, we expect that most, if any, reported injuries would result from activities unrelated to the intervention.

# 10. Data Management

## 10.1 Data Sources

All of the below data sources will be linked to our overall study data repository, which will be housed within Pedigene. PEDIGENE® is a flexible, integrated system for managing the research informatics needs for hundreds of studies and includes large databases containing clinical, pedigree, molecular, and sample data. It is an internationally acclaimed computer data management system designed and licensed by Duke, utilizing a multi-layered security system to ensure participant confidentiality through all phases of a family and population study. The Oracle database server is housed in a FISMA compliant data center and study data are accessible only by study personnel at Duke as well as authorized collaborators outside of Duke. Metabolomics, genetics, and microbiome analyses will be conducted per standards established for these kits.

### 10.1.1 EHR Data

All EHR-obtained data throughout the study duration will be linked to the main study data repository in Pedigene.

### **10.1.2 Consent/Engagement Data**

As a part of the study, participants' personal information (such as name, email address, mobile phone number, and FHIR ID which is a unique identifying number that links participants' earlier mentioned information to Mytonomy) will be shared with the Mytonomy, Inc., who is providing services for study participants to be able to view online videos, consent and surveys. All of their responses and profile information will be kept confidential in a HIPAA-compliant Data Server hosted in Amazon Web Services by Mytonomy. This protected health information is being stored so that participants can be contacted about the study and can be assisted if they contact Mytonomy for technical help. During the study period, the website registration system will also send them automatic reminder emails and text messages to complete the various steps of the study. If it appears that participants have not completed the consent, Mytonomy may contact them in order to determine if they are having technical difficulties with the system. Participant workflow through Mytonomy's online platform and data sharing plan with Mytonomy at pre-consent and post-consent time points is outlined as demonstrated in Mytonomy workflow document. These data will then flow into the overall study data repository in Pedigene.

### **10.1.3 Behavioral (Self-reported) Data**

Behavioral survey data will be collected and stored on the Mytonomy, Inc. platform, as above.

### **10.1.4 In-person Visit, Laboratory, and Imaging Data**

In-person visit, laboratory, and imaging data will be collected by the CRC and entered into a study-specific RedCap database. These data will then flow into the overall study data repository in Pedigene.

### **10.1.5 Biospecimen Data**

Data from the biospecimen analyses will be entered directly into Pedigene.

### **10.1.6 Device Data**

Data on devices provided and returned will be collected in REDCap and TRACK platform, and will then be linked to Pedigene.

### **10.1.7 TRACK Intervention Data**

The intervention environment (Track) is processed and stored on Heroku, an application server platform. This platform will support the following Track services: the Track database, SMS and IVR communications via Twilio, software logging, and file serving. The protections now in place are:

- Strong passwords and multi-factor authentication protect Web, shell, and console access to the Heroku dashboard.
- Application servers are inaccessible. These resources are virtualized and cannot be accessed via SSH or SFTP. The application itself is accessible only via SSL.
- No database configuration parameters (including host address, database name, password, and login) are stored in the application code or in the code repository.
- All Amazon services are protected. No identifiable information is stored on Amazon.
- Log files are available only through the Heroku dashboard. Log files do not reveal passwords, IP addresses, or PII. Identifying information is limited to the participant's masking study ID.
- SMS and IVR activity are protected by strong passwords.
- Further, logins to Heroku are severely restricted. Research staff does not have access to any computing resources.

Security-based software updates will be performed as needed, and logs will be monitored daily when the study launches. Only research staff who have received CITI Certification and IRB approval will have

access to the study database and information in the database will not be shared with anyone outside the research team.

## **10.2 Data Aggregation**

Data collected from the RESILIENCE Study will be available for analysis alone or in combination with other data sources for broad analysis of diverse endpoints. Data may include but is not limited to site-reported data, participant-reported data, electronic health record data, insurance claims data, laboratory data, imaging data, sensor data, data from wearable and mobile devices, environmental and other publicly available data, and third-party data. Notwithstanding the above, use of data collected from the RESILIENCE Study in combination with other sources of data relating specifically to an individual, in which the combination is intended to directly identify a participant, will require review and approval by the SC and the IRB.

## **10.3 Data Access**

It is envisioned that the RESILIENCE Study data will be available to qualified researchers for exploratory analysis in the future. Qualified external researchers may apply to use the data and samples from the RESILIENCE Study through applications reviewed by the Proposal Review and Publications Committee (Section 12.4). Biorepository sub-study will be submitted to the IRB as a separate new study application to be referred to for these applications. There will be appropriate safeguards to protect individual participant privacy.

## **10.4 Protocol Deviation Handling**

A protocol deviation is defined as an event where the Investigator or his/her delegate did not follow, intentionally or unintentionally, the specified requirements of the study protocol. There are two types of protocol deviation categories in this study: major deviations and minor deviations.

A major deviation is defined as an occurrence that resulted in an increased risk to a participant or others that affected the rights, safety, or welfare of the participant, or the integrity of the clinical study.

Examples of major deviations include, but are not limited to: failure to obtain consent prior to enrollment, or enrollment of a participant who failed to meet inclusion criteria or met exclusion criteria.

A minor protocol deviation is defined as deviating from the protocol and includes, but is not limited to: missing protocol-required tests or examinations, missed study visits, or a study visit occurring outside of the protocol-required window (early or late visit).

## **10.5 Record Retention**

Study records that identify the subject will be kept confidential as required by law. All study data will be stored and maintained in a secure manner with physical and electronic access restrictions. Access to the above mentioned files will be limited to study-key personnel who have a need to access such information. Study data generated on Mytonomy's online platform will also be stored on its HIPAA-compliant data server for at least six years after the study is finished. Per current Duke IRB guidelines, all the study records will be stored securely for six-years following completion of study. Please refer to the e-GRC section of the iRIS submission form for research data storage plan (RDSP).

# **11. Ethical Considerations**

## **11.1 Consent**

Study Informed Consent: Patients will go through the informed consent process remotely; the manner in which the informed consent information is delivered will depend on what arm they get randomized to (see Section 4.2). As part of the process, individuals will be asked questions to test their understanding of the consent material. If they answer any of these questions incorrectly, they will be prompted with the correct answer and a brief explanation. They will also have the opportunity to contact study personnel at any

point to ask questions. Once the form has been signed electronically, they will receive an electronic copy of the form, either through download/print or through email (depending on their preference).

CAC Informed Consent: Patients will go through the informed consent process for CAC testing while at their initial study visit at the South Durham clinic. This consent will be in paper form, and participants will have as much time as they need to review the form and ask any questions they have of the study coordinator. Once they have signed the form, they will receive a paper copy of the document.

### **11.2 Institutional Review Board**

The RESILIENCE study will not begin without documented approval by Duke IRB. Over the course of the study, all amendments to the protocol and ICFs will be reviewed and approved by the IRB prior to implementation, except where necessary to eliminate apparent immediate hazards to participants

### **11.3 Sharing of Data**

Participants' privacy will be protected by controlling access to sources of information that might potentially be used to identify the individual participants. Although qualified researchers may have access to data and samples from the RESILIENCE Study, proposals to use data and/or samples will require review and approval by the Proposal Review and Publications Committee. If approved, only the information necessary to perform the analyses specified in the use proposal will be released.

Biorepository sub-study will be submitted to the IRB as a separate new study application to be referred to for these applications. Additionally, Mytonomy may use the de-identified study records to analyze viewership of the videos and to provide information to third parties, such as other hospitals or healthcare entities, for the purpose of promoting or improving their services and conducting research.

### **11.4 Return of Results**

The consent form will specify what will be done in the event that life-threatening or serious health information about individual participants becomes available.

Disclosure of clinical results will be completed as follows:

- Participants may receive results from designated routine CLIA-approved clinical testing from the Investigator or his/her delegate through MyChart, mail, phone, or other methods. In addition, the study team may inform the participant's primary healthcare provider about these findings.

For all of the above, participants will be notified that these results do not serve as a substitute for usual clinical care and should see their doctor at their discretion.

The potential for harm to participants in "-omics" research has been widely discussed, with the risks of discrimination in insurance and employment receiving particular emphasis. The Genetic Information Nondiscrimination Act of 2008 addresses some of these concerns; however, less often discussed but also important are other possible harms, such as familial discord or personal psychological problems that might result from a participant receiving information about their genetic profile. Such harms arise from the disclosure of information, and the privacy protections described above should prevent unplanned disclosure of individual information.

### **11.5 Commercial Potential**

Information obtained in or generated from this project may be used to create products or material of value. Participants will not receive monetary rewards if this occurs. This will be explained in the informed consent form.

### **11.6 Compensation**

Participants will be compensated for their participation in the RESILIENCE study. The details of compensation will be provided in the informed consent form. All participants will receive \$50 after completing the first clinic visit and lab draw. Participants in the weight loss program will receive an additional \$50 upon completion of the program and lab draw at 6 months. Participants with obesity who

receive a Fitbit device as part of the study will be able to keep the device at the end of the study. Participants in CAC sub-study will receive additional \$50 and those in basic science sub-study will receive additional \$25 at both baseline and 6-month follow-up as applicable.

## **12. Study Governance**

### **12.1 Steering Committee**

The Steering Committee (SC) will provide oversight of the overall design, conduct, and supervision of the RESILIENCE Study. It will adjudicate policy issues and review the progress of the study including scientific and operational data to guide the direction of the project. The SC will be responsible for approval of amendments to the study protocol. All other committees will report into the SC.

### **12.2 Cardiometabolic Knowledge Network**

The CMKN consistent of members of the Duke community who work in the cardiometabolic space and who have an interest in participating in this and other projects in this field. The CMKN will be kept abreast of study updates and will be able to provide input that will ultimately be decided upon by the SC.

### **12.3 Patient Advisory Council**

Our patient advisory council (PAC) has been intimately involved in the governance of the RESILIENCE project, providing feedback, insight and input on elements of study design and patient-facing engagement, recruitment and retention material. Members of the PAC are key members of the project, ensuring that our focus remains patient-centered. They have been trained, empowered and encouraged to guide all aspects of the project, from study design through dissemination of the results, playing the role of both advisors and co-designers when appropriate. To date, they have participated in the development of the project title and logo, recruitment messages, consent, and video scripts for the e-consent. They will continue to provide guidance and feedback on the project through to its completion.

### **12.4 Proposal Review and Publications Committee**

The Proposal Review and Publications Committee will be the same as the SC for the duration of the study. After study completion, the SC may decide to create a separate committee to oversee this process. The Proposal Review and Publications Committee will be responsible for scientific and operational review and approval of all requests by qualified researchers for use of stored samples or data accrued by the RESILIENCE Study. Data and/or samples will not be released to a qualified researcher until this committee has approved the proposal and appropriate IRB approval has been obtained, when outside the scope of this protocol.

## **Statistical Results**

### **Research for pErSonalized cardiovascuLar dlsease prEvention, treatmeNt, and CarE Recruitment Strategies**

#### **RESILIENCE – Aim 4**

A randomized, 4-level design to determine optimal study electronic consenting methods of participants through text only, text and physician video, text and patient video, and text and animated video formats.

## **1. Overview**

### **1.1 Synopsis**

Aim 4 of the RESILIENCE study is to determine optimal methods to consent patients into the study remotely, i.e. without requiring a formal clinic visit or the direct involvement of the patient's clinician.

### **1.2 Exposure groups**

The study will be a four-level randomized design and participants will be assigned to one of four electronic consenting methods:

#1: Text only

#2: Text and physician video

#3: Text and patient video, and

#4: Text and animated video

## **2. Study Design**

### **2.1 Overview**

Invitations to participate in the study were sent to patients by email or MyChart message (See protocol section 2.2).

Upon delivery of message, participants will be given a link to access a study Mytonomy website. Once potential participants arrive at the study landing page hosted by Mytonomy, Inc. (through the eRecruitment process), they will see a brief description of the study along with an introductory video. Individuals will then be able to click on a 'Click to consent' link to begin the consent process. Consecutive individuals who click on the 'click to consent' on the 'landing' page will be randomized to consent via one of four consenting methods. Potential participants will be presented with the first page of the consent portal which will provide them IRB-approved consent form to review to sign and view one of the 4-types of consent-content mentioned above that they will be randomized to. Consenting on the study website is the primary outcome variable which will be dichotomized as consented (yes vs. no) within a 6-month period from time of invitation.

Upon signing the form each participant will be asked a total of seven comprehension questions. If the answer is incorrect the participant will be provided with the correct answer. The number of correctly answered survey questions is a secondary endpoint which will be dichotomized at several cut points.

The over-arching hypothesis is that, an informed consent form that includes both text and an animated video will lead to greater completion of the consent form and greater comprehension of the consent form compared with a text only, physician video, or patient video consent form.

### **2.2 Randomization**

Once participants click on the 'click to consent' on the 'landing page' the individuals will be assigned the consenting strategy using simple 1:1:1:1 randomization to one of four consent methods (See protocol section 4.2.2).

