### **3. Study Design**

#### **3.1 Overall Study Design**

The RESILIENCE study is a prospective study that will be conducted with 600 patients within the Duke Health System. We aim to recruit patients with 4 phenotypes: 200 patients with obesity (BMI  $\geq 30$ ) and high 10-year ASCVD risk ( $\geq 20\%$ ), 200 patients with obesity (BMI  $\geq 30$ ) and low 10-year ASCVD risk ( $< 7.5\%$ ), 100 patients with normal weight (BMI 18-25) and high 10-year ASCVD risk ( $\geq 20\%$ ), and 100 patients with normal weight (BMI 18-25) and low 10-year ASCVD risk ( $< 7.5\%$ ). We will test recruitment strategies using a 2x2 factorial design that will randomize individuals, stratified by phenotype above, to personal email vs. MyChart message, and to different message content. We will also test consenting strategies by randomizing individuals, again stratified by phenotype above, to 1 of 4 informed consent formats: text only, text + physician video, text + patient video, and text + animated video.

After consent and enrollment, baseline clinical data from the patients' electronic health record will be collected in a database. All patients will be asked to complete a series of behavioral surveys online. They will also be sent a home biospecimen collection kit, with which they will collect and return saliva and stool samples. Once the specimens have been returned, all patients will come for a visit to the Duke South Durham Clinic to have a BMI check and to have fasting labs drawn. At that point, patients with normal weight will exit the study, and patients with obesity will enter into a 6 month weight loss intervention. The intervention, called TRACK, is a proven weight loss program that utilizes health coaching and goal-setting to help patients lose weight. It is a remote intervention that is delivered entirely over their phones. The intervention will be introduced to the participants at the clinic visit, and they will receive a Fitbit and an electronic scale. At the end of the 6 month intervention, the 400 patients will be asked to collect stool specimens again with a home biospecimen kit, fill out additional behavioral surveys online, and have fasting labs drawn.

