#### 4.1.1 Electronic Recruitment: ‘eRecruitment’

Once identified as potentially eligible for the study, individuals will be assigned a recruitment/consent strategy based on block randomization of the 4 phenotypes (see Section 5.1). Two recruitment modalities and two recruitment messages will be tested in a 2x2 fashion (see Figure 1, below.).

**Figure 1.** 2 x 2 factorial randomization of method of contact and content of messages.

[figure not shown]

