#### 4.2.2 eConsent randomization

Consecutive individuals who click on the ‘click to consent’ on the ‘landing’ page will be randomized to consent via one of four methods: a) video consent with study information provided by patient, b) video consent with study information provided by doctor, c) video consent with study information provided by animation/cartoon or d) text-based study information and consent (standard of care).

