#### 3.4 Multiplicity Adjustments

Multiplicity will be controlled at  $\alpha=0.05$  for the statistical tests associated with the primary objective. A single interim analysis of the primary endpoint was conducted at  $\alpha=0.01$ , leaving the remaining  $\alpha=0.04$  for the final analysis. A global 3 df hypothesis test of any difference between the four consenting strategies will be tested at  $\alpha=0.04$ , and confidence intervals for effect estimates for the primary endpoint (relative risks) will be reported with nominal 96% confidence. Multiplicity will not be controlled between the primary and secondary endpoint analyses, and the secondary endpoint will be tested at  $\alpha=0.05$ , and effect estimates reported with nominal 95% confidence intervals. Subgroup analyses for the primary

endpoint will be considered exploratory, with interactions tested at nominal  $\alpha=0.05$ . All other estimates will be reported with nominal 95% confidence limits.

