## 9. Primary Endpoint Analyses

### 9.1 – Primary Endpoint: Descriptive Summaries

Endpoint Description: Electronically consenting on the Mytonomy website dichotomized as yes vs. no.

Additional Stratification Factors: None

Statistical Tests:

The total number of consented participants and the total number of participants who landed on the Mytonomy website will be reported for all intervention groups using a binomial distribution with a normal approximation (i.e., Wald confidence limits) the proportion and 95% CI for consenting on the Mytonomy website will be reported.

Report:

Risk group and exposure groups will be enumerated and the proportion and 95% CI for landing will be reported. For patients who consented, the time from landing to consent will be summarized with descriptive statistics. [Tables 2a](#), [Table 2b](#)

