### 9.2 – Primary Endpoint: Inferential Analyses

Endpoint Description: Electronically consenting on the Mytonomy website dichotomized as yes vs. no.

Statistical Tests:

A robust log linear Poisson model will be used for modeling electronically consenting on the Mytonomy website vs. not as a function of consenting method to find the relative risk/risk ratio (RR) of consenting. The model will be fit using Generalized Estimating Equations (GEE) to provide a robust estimates of the covariance. The hypothesis of no difference between exposure groups will be tested using the global test p-value for consenting method (3 df Wald test). A p-value  $< 0.04$  will be considered statistically significant evidence of at least one difference between groups. Pairwise comparisons between consenting methods will be made using relative risks (96% confidence intervals), with 'Text Only' as the reference category.

Report:

The associations between the consenting methods will be characterized by each groups as RR, the corresponding 96% confidence interval, and global p-value. [Table 3](#)

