### 9.3 – Primary Endpoint: Subgroup Analyses

Endpoint Description: Electronically consenting on the Mytonomy website dichotomized as yes vs. no.

Sub-groups: Age at randomization, sex, race and risk group phenotypes.

Statistical Tests:

A robust log linear Poisson model will be used for modeling electronically consenting on the Mytonomy website vs. not will be modeled as a function of the exposure group (main effect), subgroup and the interaction between exposure group x subgroup.

Report:

The associations will be characterized by RR (95% CI) for each consenting method within each subgroup. The p-value for the interaction effect will test whether differences in consenting between exposure groups, differs by subgroup. [Table 4](#), [Figure 2](#)

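### Protocol and SAP disagree on whether consent randomisation was stratified by phenotype, and the primary model omits phenotype; the effect is small and does not change the primary conclusion.

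*Combined protocol and SAP*

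**What the plan says.** The documents describe one randomisation in four ways.

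- Protocol 3.1, and the synopsis in near-identical terms: "We will also test consenting strategies by randomizing individuals, again stratified by phenotype above, to 1 of 4 informed consent formats".
- Protocol 4.1.1, for people just identified as potentially eligible and so before any contact: "individuals will be assigned a recruitment/consent strategy based on block randomization of the 4 phenotypes". It refers to Section 5.1 for detail, but 5.1 covers clinical data from the health record.
- Protocol 4.2.2: "Consecutive individuals who click on the ‘click to consent’ on the ‘landing’ page will be randomized to consent via one of four methods". It mentions neither strata nor blocks.
- SAP 2.2, citing protocol 4.2.2: "the individuals will be assigned the consenting strategy using simple 1:1:1:1 randomization to one of four consent methods".

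SAP 9.2 models consent "as a function of consenting method to find the relative risk/risk ratio (RR) of consenting", with no other term. The model for the comprehension endpoint in SAP 10.2 has the same form. Phenotype enters only the subgroup and interaction models, for example in SAP 9.3: "Sub-groups: Age at randomization, sex, race and risk group phenotypes". SAP 3.4 and 9.2 set the final significance level for the global 3-df test at 0.04.

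**The concern.** Two features of the allocation are in conflict: the method (stratified or blocked, against simple) and the moment (at identification, against at the click). The SAP records no departure from protocol 3.1 or 4.1.1.

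This matters for the analysis because the usual rule is that the model reflects the allocation. If phenotype was a stratification factor, a model without it overstates the standard errors. If allocation was simple, the unadjusted model is valid, but a baseline variable held for all 1,535 participants goes unused and chance imbalance in it stays in the estimates. Either consequence grows with the strength of the link between phenotype and consent. The documents never print that link, because Table 4 gives only between-arm ratios within each phenotype.

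**Working it through.** **1. Reproduce the printed primary result.** Table 2a gives consents of 241/386 (physician video), 203/383 (patient video), 223/386 (animated video) and 221/380 (text only). For the arm-only robust Poisson model, SE(log RR) = √(1/x₁ − 1/n₁ + 1/x₀ − 1/n₀). For patient video, RR = (203/383)/(221/380) = 0.911 and SE = 0.0649. The global Wald statistic is 6.97 on 3 df, p = 0.073. This agrees with the 0.07 and the three ratios in Table 3.

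**2. Recover consent counts by phenotype.** Denominators come from Table 1. For each phenotype, every pair of text-only count and video-arm count was tried. A pair was kept if its RR and 95% limits, RR × exp(±1.96 SE), matched Table 4 to the printed digits. Example, obese high risk, physician video: (91/138)/(72/125) = 1.14, SE = 0.098, limits 0.94 to 1.39, as printed.

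| Phenotype | Physician | Patient | Animated | Text | Consent |
|---|---|---|---|---|---|
| Obese high | 91/138 | 74/140 | 85/138 | 72/125 | 322/541 = 59.5% |
| Obese low | 86/116 | 64/107 | 75/109 | 78/122 | 303/454 = 66.7% |
| Non-obese high | 26/44 | 30/38 | 30/49 | 34/49 | 120/180 = 66.7% |
| Non-obese low | 38/88 | 35/98 | 33/90 | 37/84 | 143/360 = 39.7% |

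One text-only count per phenotype fits all the usable cells. The patient, animated and text columns sum to 203, 223 and 221, exactly as in Table 2a. Eleven of the 12 Table 4 phenotype cells match. The exception is obese low risk, physician video, printed as 1.13 (0.75, 1.71). No count fits it, so 86 is the remainder, 241 − 91 − 26 − 38, and it gives 1.16 (0.98, 1.38). The interaction p from these counts is 0.15, against 0.2 printed.

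**3. Strength of phenotype.** Chi-square is 69.6 on 3 df. As a share of outcome variance, that is 69.6/1,535 = 4.5%.

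**4. Refit with phenotype added.**

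| Against text only | Arm only: RR (96% CI), SE | With phenotype: RR (96% CI), SE |
|---|---|---|
| Physician | 1.074 (0.952, 1.211), 0.0588 | 1.081 (0.960, 1.217), 0.0578 |
| Patient | 0.911 (0.798, 1.041), 0.0649 | 0.930 (0.816, 1.060), 0.0637 |
| Animated | 0.993 (0.875, 1.127), 0.0615 | 1.002 (0.886, 1.135), 0.0603 |
| Global test, 3 df | 6.97, p = 0.073 | 6.23, p = 0.101 |

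Standard errors fall by about 2%. A Cochran–Mantel–Haenszel test stratified by phenotype gives p = 0.105.

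**5. Why patient video moves most.** Non-obese low risk, the phenotype that consents least, is 98/383 = 25.6% of that arm and 84/380 = 22.1% of text only. Applying the four overall phenotype rates to each arm's mix gives expected consent of 219.0/383 = 57.2% for patient video and 221.9/380 = 58.4% for text only, a ratio of 0.979. Then 0.911/0.979 = 0.93, the adjusted figure.

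**6. Error rate of the unadjusted test at 0.04.** In 20,000 simulated trials with the phenotype totals and rates above, it is 0.041 under simple allocation and 0.036 when arms are balanced within phenotype. The large-sample value for the balanced case is 0.033, from referring 8.31/(1 − 0.0453) = 8.71 to chi-square on 3 df.

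**7. What Table 1 suggests about the scheme.** Arm sizes within phenotype range over 125–140, 107–122, 38–49 and 84–98, differences of 15, 15, 11 and 14. The phenotype-by-arm chi-square is 5.23 on 9 df, p = 0.81.

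**The case against.** The best reply is that this is a documentation fault with little statistical consequence, and most of that stands. Under simple allocation the unadjusted test holds its level. Under stratification it errs on the safe side. The gain in precision is about 2%, and the spread in consent comes mainly from one phenotype. The Table 1 differences of 11 to 15 are what simple allocation would produce; small blocks applied at the click would have kept arm sizes closer. That supports SAP 2.2 but does not settle the matter. Exclusions, or blocking all invitees and then analysing only those who clicked, could leave the same pattern.

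Four stronger readings are tempting, and the documents do not support them.

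- *With p near its threshold, the choice of model decides the answer.* It does not: 0.073 and 0.101 both exceed 0.04, adjustment moves p away from the threshold, and every 96% interval includes 1 in both models.
- *Phenotype should enter the primary model whichever scheme was used.* Invitations ended in March 2022 and the tables carry dates from December 2023 to January 2024. Replacing the stated primary test now is a change made with results in hand, and only the design could justify it.
- *The comprehension model loses precision in the same way.* Everything above concerns consent. Nothing here shows that phenotype predicts quiz score.
- *SAP 9.1 confirms unstratified allocation.* Its line "Additional Stratification Factors: None" belongs to the descriptive summaries and says nothing about how people were allocated.

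**Conclusion.** The contradiction on method and timing is explicit, and only the sponsor can resolve it. Its numerical effect is modest: relative risks shift by 0.01 to 0.02, and the primary result is non-significant at 0.04 under either model. If allocation was stratified, the unadjusted test is slightly conservative. If it was simple, the test is valid, slightly less precise, and leaves a chance phenotype imbalance that makes patient video look a little worse than it does after adjustment.

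The size rests on reconstructed counts, with one cell taken as a remainder. The 0.036 assumes balance within phenotype among the people analysed. Blocking at identification, with few invitees going on to click, would give less balance than that and an error rate nearer to the nominal level.

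**What to change.** 1. State the allocation method and its timing as actually carried out, in the same words in the synopsis, protocol 3.1, 4.1.1 and 4.2.2, and SAP 2.2.
2. If allocation was stratified by phenotype, include the four-level phenotype in the SAP 9.2 model and, as the design factor, in 10.2. Show the unadjusted results beside it.
3. If allocation was simple, record the departure from the protocol and keep the stated unadjusted test as primary. Report the phenotype-adjusted relative risks and global test beside it as a sensitivity analysis, labelled as added after results were known.
4. Check the obese low risk, physician video cell of Table 4 against the data, and print consent counts by phenotype and arm.

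The cost is wording and one re-run, with no new data. The addition is not entirely free, because results are known; hence the label in step 3.
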